**Figure 3 jan14517-fig-0003:**
[figure not shown]
ISP program and its five modules. Note: TA, Technical assistants; ISP, Internet‐based support program [Colour figure can be viewed at wileyonlinelibrary.com]

The researchers will teach women in the intervention group how to log in and use each module of ISP by mobile phone or computer. The original username and password of women will be setup by the researchers; and can be changed by women later. The frequency and duration of the logins will be monitored to evaluate the women's adherence. Technical assistance will be available on the weekdays by telephone or email.

#### Outcome measurements

3.2.6

##### Primary outcomes

###### MSE

*MSE* will be evaluated by the Self‐efficacy in Infant Care Scale (SICS) (Prasopkittikun & Tilokskulchai, 2010). The SICS is a 46‐item scale comprising of four dimensions. Each item indicates one parenting task rated from 0 to 100 points. A higher SICS score means a higher level of *MSE*. The SICS has demonstrated good psychometric properties. The reported internal consistency was 0.96 for the total scale and ranged from 0.86 to 0.96 for its dimensions (Prasopkittikun & Tilokskulchai, 2010). In terms of Chinese version SICS, its Content Validity Index (CVI) was 0.98; and the internal consistency was 0.95 for the scale and was in range 0.80–0.93 for its dimensions (Zang & Sheng, 2010).

###### PPD

PPD will be assessed using the Edinburgh Postnatal Depression Scale (EPDS) (Cox, Holden, & Sagovsky, 1987). The scale is a 10‐item 4‐point Likert instrument to detect PPD. The self‐report scale's score ranges between 0 and 30 and the higher score indicates the worse health status women have. The EPDS has demonstrated good reliability and validity. The Cronbach's alpha coefficient of the Chinese version EPDS was 0.87; and the concurrent validity with the Beck Depression Inventory was 0.79 (Wang et al., 2009).

###### Social support

Postnatal social support will be measured using the Postpartum Social Support Scale (PSSS), developed for Chinese women to measure their perceived social support after childbirth (Lu & Zheng, 2001). The scale is a 20‐item four Likert self‐report tool and its score is in range 0–60 overall. The higher score equates to the more social support a mother receives. The Cronbach's alpha coefficient of PSSS was 0.89 and the content validity of this tool was 0.90 (Lu & Zheng, 2001).

##### Secondary outcomes

###### Satisfaction with healthcare

Women's satisfaction with health care after childbirth will be assessed with a 3‐item questionnaire developed by the researcher. For instance, “Overall, how satisfied you are with the healthcare?”, “Please give your reasons”, and “Please give your suggestions”.

##### Other outcomes

###### Social‐demographic and clinical data

The collected data comprise the maternal age, marital status, educational level, occupation, family income, mode of birth, baby gender, baby health, and baby fussiness via women's self‐report.

###### Internet usage data for the ISP

Internet use data, such as the frequency and duration of logins and the website activity of each module of the ISP, will be recorded and evaluated by a tracking system from the website.

#### Data collection procedure

3.2.7

The baseline assessment will be conducted by the researchers and every participant will be asked to complete the SICS, EPDS, PSSS, and social‐demographic and clinical data in the obstetric wards. Post‐test 1 will be carried out immediately after the intervention and Post‐test 2 will be conducted on 3 months after the intervention. At the two time points of Post‐tests 1 and 2, the questionnaires comprised of SICS, EPDS, PSSS, and healthcare satisfaction will be sent to participants by wechat or email; and the completed questionnaires will be returned to the researchers by wechat or email. To improve the response rate, a kindly telephone or wechat reminder will be given to participants before and after one week of the two time points, respectively.

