#### Randomization and blinding

3.2.4

The Research Randomizer will be used to randomly assign participants into the experimental group and the control group with a distribution ratio of 1:1. The allocation sequence will be put into the opaque and sealed envelopes. Blinding will not be possible for the researchers during all the research process; however, the group allocation will be masked during the recruitment until the baseline measures are completed. In terms of trial participants, outcome assessors, and data analysts, they will be blinded to the participants’ group allocation.

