#### Intervention

3.2.5

The women in the control group will receive routine care. Routine care consists of supports from the obstetricians and obstetric nurses during the 3–5 days hospitalization; and home visits from the community doctors on the 3rd, 7th, 14th, and 28th days postpartum (Zheng, Morrell, & Watts, 2015). The women in the study group will have access to the ISP and receive routine care in the postpartum period. The details of intervention are described in Table 1.

**Table 1 jan14517-tbl-0001:** The details of intervention

	Intervention Group	Control Group
Service	ISP + routine care	Routine care
Provider	Researchers	Obstetricians, obstetric nurses, community doctors
Place	Web environment	Hospital, home
Form	Internet	Face‐to‐face
Contents	Learning forum Communication forum Ask‐the‐expert forum Baby home forum Reminder forum	Routine postpartum home visiting
Duration and frequency	From childbirth to 3‐month postpartum The total intervention time not less than 12 weeks Reminder telephones every week, reminding them to log in the ISP at least twice a week, and no less than total 1 hr per week	From childbirth to 1 month postpartum At least two home visits
Assessment	Baseline (pre‐intervention) Post‐test 1 (immediately after intervention) Post‐test 2 (3 months after intervention)	Baseline (pre‐intervention) Post‐test 1 (immediately after intervention) Post‐test 2 (3 months after intervention)

Abbreviations: ISP, Internet‐based Support Program.

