### Ethical considerations

3.3

Research ethical committee approval is obtained by the Research Ethics Committee of Health Science Center in a University of China (approval number 2,020,011). The registration number with the Chinese Clinical Trial Registry is ChiCTR2000033154. This study will adhere to ethical standards for the whole procedure. There is no potential risk or harm by participating in this program. Women will not be deprived of any treatment and routine care. The written informed consent will be obtained from every participant before data collection. Women will be informed of freedom to withdraw at any time and are assured of anonymity by using special code numbers to identify themselves. All of the collected data will be kept anonymously and confidentially.

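### Both post-tests send identifiable self-report forms back to the unblinded researchers who provide the ISP, a route by which reporting could differ between arms

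*Protocol article*

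**What the plan says.** **Collection of outcomes (3.2.7).** At post-tests 1 and 2 the three scales and the satisfaction questions go out electronically. The return route is given as follows: "the completed questionnaires will be returned to the researchers by wechat or email". No other recipient is named.

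**Who delivers the ISP (3.2.5).** For the intervention group, Table 1 reads "Provider Researchers". Control care comes from obstetricians, obstetric nurses and community doctors. After Figure 3 the section adds: "The researchers will teach women in the intervention group how to log in and use each module of ISP by mobile phone or computer". The researchers also set up each woman's login. Table 1 gives the intervention arm weekly telephone prompts: "Reminder telephones every week, reminding them to log in the ISP at least twice a week". The caller is not identified.

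**Blinding (3.2.4).** "Blinding will not be possible for the researchers during all the research process". Participants, outcome assessors and data analysts are said to be blinded, and 3.4 repeats this for assessors and analysts.

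**Anonymity (3.3).** Women are "assured of anonymity by using special code numbers to identify themselves", and the section adds that all data are kept anonymously and confidentially.

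**The concern.** All three primary outcomes and the satisfaction outcome are the woman's own answers, so anything that shifts how she answers goes straight into the data. Under 3.2.7 she sends those answers, by a channel that shows her as the sender, to the group that supplied the programme under test and taught her to use it. A control woman sends hers to the same group, but has had less to do with them. If courtesy or the wish to please grows with that contact, the arms would report differently for a reason other than the effect of the ISP. Blinding the analyst cannot take such a shift out of answers already given.

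A second, smaller matter is the wording. Women are told that their depression answers are anonymous, while the procedure lets the recipient see who sent them and needs a link between three assessments.

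**Working it through.** The plan gives no figure on this point, so the first check sets the sections side by side. The arithmetic after it shows scale only.

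**1. The chain from answer to recipient**

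| Step | Section | What is stated |
|---|---|---|
| Outcomes | 3.2.6 | EPDS and PSSS are described as self-report. SICS and satisfaction are also questionnaires completed by the women |
| Route | 3.2.7 | WeChat or email, both post-tests |
| Recipient | 3.2.7 | The researchers |
| Recipient's blinding | 3.2.4 | None, at any stage |
| Recipient's role in the intervention arm | 3.2.5, Table 1 | Provider, trainer, account set-up |
| Recipient's role in both arms | 3.2.3, 3.2.7 | Information, consent, baseline assessment |

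In addition, Module 5 of the ISP (3.2.5) contains a reminder to fill in the questionnaires, so in the intervention arm the programme being judged also prompts the outcome forms. Contact with the recipients is therefore unequal: it is present in both arms and greater in the intervention arm.

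**2. Anonymity wording**

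Section 3.3 ties anonymity to code numbers. Section 3.2.7 needs reminders to reach each woman, and the analysis in 3.2.8 needs her three assessments linked. Data of that kind are coded and confidential, which is not the same as anonymous.

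**3. How large a shift would matter**

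Inputs from the documents: EPDS means of 6.87 and 5.61 with SDs of 3.97 and 3.33 in the earlier trial (Introduction), and a planned effect of 0.35 SD with 90 per group before attrition and 129 per group recruited (3.2.2). The shifts are assumptions.

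- Earlier difference: 6.87 − 5.61 = 1.26 points.
- Pooled SD: √((3.33² + 3.97²)/2) = 3.66. The planned effect is then 0.35 × 3.66 = 1.28 points, so 1.26 is a fair stand-in.
- Assumed differential shift as a share of 1.26: 0.25/1.26 = 20%; 0.5/1.26 = 40%; 1/1.26 = 79%.

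Rejection rate of a two-sided 0.05 test when the ISP has no true effect but reporting differs by *b* SD (normal approximation, simple comparison of two means):

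rate = Φ(b/SE − 1.96) + Φ(−b/SE − 1.96), with SE = √(2/n).

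| Assumed b (SD) | EPDS points | n = 90 per group | n = 129 per group |
|---|---|---|---|
| 0.1 | 0.37 | 10% | 13% |
| 0.2 | 0.73 | 27% | 36% |
| 0.3 | 1.10 | 52% | 67% |

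The planned analysis is a repeated measures MANCOVA, so these rates illustrate sensitivity and do not predict the trial's error rate.

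**The case against.** Several stronger readings are tempting, and the documents do not support them.

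- *The return route breaks the promise of anonymity.* A reader might infer this, but 3.3 says that anonymity is achieved by code numbers, and its second statement concerns how data are kept. A form sent by WeChat or email can carry a code and be stored coded. The wording is loose; the promise is not shown to be broken.
- *The women use personal accounts.* The article names only WeChat or email. It does not say whose accounts these are, or whether the form is an attachment or a link.
- *The bias acts in one arm only.* Researchers also approach, consent and assess control women at baseline (3.2.3, 3.2.7). The difference is one of degree.
- *Every scale must move towards the hypothesis.* Closer contact could also lead to franker disclosure of symptoms. A shift in favour of the ISP is plausible, not demonstrated.

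Three further points have weight. *Researchers* is a team label, and 3.2.4 and 3.4 state that assessors and analysts are blinded, so roles may be partly separated. The limitations (4.1) concede that unblinded researchers may introduce bias, although the remedies named there, an attrition allowance and ITT, address loss to follow-up. Finally, an article may leave operational detail to a full protocol. That does not dispose of the point, because the article states both the recipient and the route; they are not missing.

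**Conclusion.** The point holds in a limited form, as a cheap improvement and not as a fatal flaw. The stated procedure returns identifiable self-reports on every primary outcome, and on satisfaction, to unblinded people who provide the ISP and have more contact with one arm. That is a real route for differential reporting, plausibly in favour of the ISP. Its size is unknown. The figures of 20% to 79% of a 1.26-point difference rest wholly on assumed shifts of 0.25 to 1 EPDS point. They do not separate the return route from the wider effect of women knowing that they received the programme. The wording on anonymity in 3.3 needs correcting, but is not evidence of a broken assurance.

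**What to change.** 1. In 3.2.7, use WeChat or email only to send the invitation, with a link to an online form opened by study code.
2. Send replies to a data file that those delivering the ISP cannot see. They see only whether a form has been completed.
3. Tell women in both arms, in the invitation, who will and will not see their answers.
4. Withhold the free-text satisfaction answers (reasons and suggestions, 3.2.6) from the blinded analysts until the scale analyses are done, since intervention women may mention the ISP there.
5. In 3.3, replace *anonymously* with *coded and confidential*, and align the assurance given to women.

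The cost is setting up a standard online form, a separately held list linking codes to women, and a short change of wording. No extra staff or visits are needed. The change does not remove bias from women knowing their own allocation.

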#### Data analysis

3.2.8

Data will be analysed using the Statistical Package for Social Sciences (SPSS). An intention‐to‐treat analysis (ITT) will be adopted to manage missing data. Descriptive statistics were conducted to describe the sociodemographic and clinical characteristics of primiparous women by means and standard deviations (SDs); frequencies and proportions. The chi‐square (χ2) and the independent sample *t* test will be used to detect any significant difference between the study and control groups on the baseline variables. Adjusted for possible confounding factors of sociodemographic variables, the repeated measures triply MANCOVA will be conducted to determine whether the intervention of ISP is effective in enhancing *MSE* and social support and for reducing PPD across the three time points of data collection (baseline, post‐test 1, and post‐test 2). The independent *t* test will be used to compare how satisfied the intervention group and the control group are with the health care that they received after childbirth on the two time points of immediately after the intervention and 12 weeks after intervention.

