#### Study setting and participants

3.2.2

The research will be carried out in the two university‐affiliated tertiary public hospitals in China, where the live births in each study hospital are over 2,000 babies per year. The inclusion criteria will be: first‐time mothers with healthy babies; aged 18 years or above; married; and able to response the questionnaires. Exclusion criteria will be: women or their children have severe physical and mental diseases.

Sample size will be estimated based on previous research with a medium to small effect size (Cohen, 1992). With a power of 0.80, an alpha set at 0.05, and an effect size of 0.35 for the primary outcome of PPD (EPDS scores), each group will be 90 women (Gao et al., 2012). We estimate a 30% attrition rate based on an attrition rate of 9%–29% in previous research (Gao et al., 2012). A minimum of 258 women (129 in each group) are required.

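### Baseline significance tests and an open set of 'possible confounding' covariates should give way to prespecified adjustment for each outcome's baseline score; the cost is power, not validity

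*Protocol article*

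**What the plan says.** Section 3.2.8 (Data analysis) contains three relevant statements.

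- Chi-square and independent t "test will be used to detect any significant difference between the study and control groups on the baseline variables".
- The main model, a repeated measures triply MANCOVA, is "Adjusted for possible confounding factors of sociodemographic variables". No variable is named and no selection rule is given.
- The intervention effect on self-efficacy, social support and depression is judged "across the three time points of data collection (baseline, post"-test 1 and post-test 2). Baseline is therefore one of three response occasions. It is not described as a covariate.

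The baseline data come from two places. The section on social-demographic and clinical data lists "the maternal age, marital status, educational level, occupation, family income, mode of birth, baby gender, baby health, and baby fussiness", which is nine variables. In section 3.2.7 "every participant will be asked to complete the SICS, EPDS, PSSS" at baseline, which adds three scale scores. Section 3.2.2 restricts entry to women who are "aged 18 years or above; married" and have healthy babies, and places the trial in two university-affiliated "tertiary public hospitals in China". Section 3.2.4 describes 1:1 random assignment and mentions no stratification.

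**The concern.** A test of baseline equality between randomised groups has a null hypothesis that is true by design. A small p-value shows chance at work and says nothing about whether the variable matters for the outcome. Such tests should not steer an analysis.

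The next sentence then adjusts for possible confounders. In a randomised comparison, baseline confounding can only mean chance imbalance. The wording therefore nudges the analyst towards choosing covariates by how unbalanced they look, not by how well they predict the outcome.

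Meanwhile the variables most likely to predict each outcome, its own baseline scores, serve only as a response level. A group-by-time test on baseline and two post-tests spends information on a baseline contrast that is known to be zero in expectation. A group main effect averages that zero into the treatment effect. Power is at stake in both cases.

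**Working it through.** The plan gives no figure on this point to reproduce. All results below are for one outcome at a time. The joint test of three outcomes also depends on the correlations between them, which the article does not give.

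**1. Chance of a spurious baseline difference.** The number of variables is 9 + 3 = 12. Eligibility fixes marital status and largely fixes baby health, leaving 11 or 10. With independent tests at 0.05 the chance of at least one significant result is 1 − 0.95^k:

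- k = 12: 0.46
- k = 11: 0.43
- k = 10: 0.40

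Positive correlation between variables would lower these values. They give the chance of any spurious difference, not the chance that a covariate enters the model. Read strictly, the sociodemographic variables that can vary are age, education, occupation and income: 1 − 0.95^4 = 0.19.

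**2. If imbalance tests did choose the covariate.** This was simulated with 180 women, d = 0.35 and 8,000 runs. The covariate was kept only if its baseline test gave p < 0.05, and this rule was compared with always including it. The correlations with the outcome are assumed.

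| Correlation | Type I error, test-driven | Power, test-driven | Power, prespecified |
|---|---|---|---|
| 0.3 | 0.047 | 0.63 | 0.67 |
| 0.5 | 0.044 | 0.66 | 0.77 |
| 0.7 | 0.036 | 0.66 | 0.91 |

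The rule is slightly conservative and gives up most of the gain from adjustment.

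**3. Baseline as response level or as covariate.** The inputs from section 3.2.2 are n = 90 per arm, d = 0.35 and alpha 0.05 (taken as two-sided). I assume equal correlation r between all occasions, unit variance, and the same effect at both post-tests. Let s = √(n/2) = √45 = 6.71.

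- Baseline-adjusted, one post-test: non-centrality 0.35·s/√(1 − r²).
- Baseline-adjusted, mean of both post-tests: 0.35·s/√v with v = (1 + r)/2 − r², which is 0.56, 0.50 and 0.36.
- Group-by-time over three occasions: effects are 0, 0.35 and 0.35, and the sum of squares about their mean is 2(0.35²)/3 = 0.0817. Then λ = 45 × 0.0817/(1 − r) = 5.25, 7.35 and 12.25, on 2 and 356 df.
- Group main effect over three occasions: the mean effect is 2(0.35)/3 = 0.233, with variance (1 + 2r)/3.
- Mean of post-tests minus baseline, 1 df: 0.35·s/√(1.5(1 − r)).

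| Power | r = 0.3 | r = 0.5 | r = 0.7 |
|---|---|---|---|
| Adjusted, one post-test | 0.69 | 0.77 | 0.91 |
| Adjusted, mean of both post-tests | 0.88 | 0.91 | 0.97 |
| Group-by-time, three occasions | 0.52 | 0.67 | 0.89 |
| Group main effect, three occasions | 0.57 | 0.48 | 0.41 |
| Mean of post-tests minus baseline | 0.63 | 0.77 | 0.94 |

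Simulation of the first, third and fourth rows agrees to within 0.02 (0.67/0.77/0.91, 0.52/0.68/0.89 and 0.56/0.48/0.42). The like-for-like comparison, using both post-tests, is the second row against the last three.

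**4. Hospital.** I assume the hospital accounts for 1%, 5% or 10% of outcome variance, with equal recruitment and unstratified allocation. Leaving out the term keeps type I error at about 0.05. Adding it moves power from 0.64/0.64/0.65 to 0.64/0.66/0.69.

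**The case against.** The article never connects the baseline tests with the choice of covariates. The two sentences are adjacent, but their scope differs: the tests cover all baseline variables and the adjustment covers sociodemographic ones. A covariate list is also something a condensed article may leave to the full plan. Data analysts are to be blinded (sections 3.2.4 and 3.4), which limits steering towards one arm. All of this stands. A reader might infer selection by p-value, but the text only invites it.

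A reader might also infer that inference becomes anti-conservative. The simulation shows the reverse for a fixed p < 0.05 rule. Inflation would need covariates chosen with sight of the outcome, and nothing in the article suggests that.

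It is tempting to say that the baseline scores are missed. They are not: they are in the model as a time level, and the objection is only to efficiency. Nor does the article exclude a hospital term. It is silent, and the stakes are small. Marital status is merely listed as collected data, and recording an eligibility characteristic is no error.

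What the objection does not remove is that the tests are explicitly planned and uninformative, and that baseline is explicitly placed in the response. A fuller plan could correct these choices, but it could not justify the tests.

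**Conclusion.** The point holds in a limited form. The baseline tests serve no purpose, the adjustment set is framed in a way that invites imbalance-driven choices, and the stated use of baseline scores is less efficient than adjusting for them.

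Using both post-tests with baseline adjustment raises single-outcome power over the three-occasion group-by-time test by about 0.36, 0.24 and 0.09 at correlations of 0.3, 0.5 and 0.7 (0.88 − 0.52, 0.91 − 0.67, 0.97 − 0.89 with unrounded values). Against a focused change contrast the gain is smaller: 0.25, 0.14 and 0.04.

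These sizes rest on assumed correlations, a constant effect at both post-tests, and the plan's 90 analysable women per arm. They do not bear on whether 90 is the right number, which is a separate question. The planned analysis remains valid in type I error. The 40–46% figure should be quoted only as the chance of some spurious baseline difference under independence.

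**What to change.** - Present baseline characteristics by arm descriptively and drop the p-values.
- For SICS, EPDS and PSSS, take post-test 1 and post-test 2 as the response and include that outcome's baseline score as a prespecified covariate. Remove baseline from the response, so that it is not used on both sides of the model.
- Name any further covariates before unblinding, on prognostic grounds, and keep them whatever the observed imbalance.
- Report the unadjusted estimate as a sensitivity analysis.
- Optionally add hospital, at one degree of freedom and with little expected gain.

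This changes the main model from three response occasions to two plus a covariate, so it is more than a change of label. It needs no new data, because every variable is already collected or known, and it alters no design or sample-size figure.

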### Aim

3.1

This study aims to evaluate the effects of ISP for Chinese primiparous women in terms of improving the levels of *MSE*, social support, and satisfaction; and reducing their postpartum depression symptoms.

The study hypothesizes that compared with the control group at baseline, post‐test 1, and post‐test 2, women in the intervention group will report statistically significant:
Improved *MSE* and social support;Reduced postpartum depression symptoms; and.Great satisfaction with healthcare received after childbirth.

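### The one test named for the three primary outcomes is a joint MANCOVA, so a significant result does not show which scale changed or when, and it is not a test of the EPDS difference on which the trial is sized

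*Protocol article*

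**What the plan says.** Section 3.1 (Aim) lists the hypotheses outcome by outcome: "Improved *MSE* and social support;Reduced postpartum depression symptoms; and.Great satisfaction with healthcare received after childbirth". Section 3.2.6 gives self-efficacy (SICS), depression (EPDS) and social support (PSSS) as primary outcomes, and satisfaction as secondary.

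Section 3.2.8 (Data analysis) assigns the three primary outcomes to one procedure. After the words "Adjusted for possible confounding factors of sociodemographic variables", it states that "the repeated measures triply MANCOVA will be conducted to determine whether the intervention of ISP is effective in enhancing" self-efficacy "and social support and for reducing PPD across the three time points of data collection (baseline, post‐test 1, and post‐test 2"). It does not say whether the group effect or the group-by-time effect decides. The only other between-arm outcome test concerns the secondary outcome: "The independent *t* test will be used to compare how satisfied the intervention group and the control group are with the health care".

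Section 3.2.2 sizes the trial on one scale: "an effect size of 0.35 for the primary outcome of PPD (EPDS scores), each group will be 90 women". Allowing for 30% attrition, this becomes 129 per group, 258 in all.

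**The concern.** The aim asks three questions, one per outcome, and the sample size is built on one of them. The analysis section answers all three with a test that addresses none of them singly. A triply multivariate test has one null hypothesis: every between-arm effect in the tested set, over all three scales, is zero. Any departure, on any scale or combination of scales, can cause rejection.

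If the sentence is followed literally, a significant result counts as evidence for "Reduced postpartum depression symptoms" even when EPDS has not moved and the signal comes from self-efficacy or social support. Depression is the outcome used to size the trial. The Discussion and Conclusion foresee routine use of the programme if results are positive, so an unsupported depression claim would carry weight.

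**Working it through.** **The plan's own figure.** The 0.35 is a standardised between-arm difference on EPDS alone. The two-sided two-sample formula gives n = 2(1.960 + 0.842)²/0.35² ≈ 128.2, so 129 evaluable per group; one-sided it gives 101. The stated 90 is not reproduced. With 90 per group, power is 65% two-sided or 76% one-sided. The attrition step does reproduce: 90/0.70 = 128.6, so 129. The shortfall is a separate matter and nothing below depends on it. What matters here is that the sizing calculation refers to an EPDS contrast that section 3.2.8 does not name.

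**Inputs for the omnibus test.** From the article: three scales, three times, 1:1 allocation, alpha 0.05, 90 completers per arm. Assumed, because the article gives no figures: correlation r between scales 0.3 or 0.5 (EPDS reversed so that higher is better), correlation ρ over time 0.4 or 0.6, no covariates, effects equal at both post-tests and zero at baseline. As the article does not say which effect is tested, both are shown.

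**Formula.** For two groups, the multivariate test is Hotelling's T², with power from the noncentral F distribution. The noncentrality is λ = (n/2)·δ′Σ⁻¹δ, with p and 2n − p − 1 degrees of freedom. Under the assumed covariance it factors as λ = (n/2)·s·t.

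- Scale part, with SICS and PSSS better by 0.35 and EPDS zero: s = 2(0.35²)/[(1 − r)(1 + 2r)]. This is 0.245/1.12 = 0.219 for r = 0.3, and 0.245/1.00 = 0.245 for r = 0.5.
- Time part, group by time (p = 6, df 6 and 173): t = (2/3)/(1 − ρ), which is 1.111 for ρ = 0.4 and 1.667 for ρ = 0.6.
- Time part, group (p = 3, df 3 and 176, mean over the three times): t = (4/3)/(1 + 2ρ), which is 0.741 and 0.606.

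**Results with no EPDS effect, n = 90 per arm (n/2 = 45).**

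| r | ρ | λ, group by time | Rejects | λ, group | Rejects |
|---|---|---|---|---|---|
| 0.3 | 0.4 | 10.9 | 67% | 7.3 | 60% |
| 0.3 | 0.6 | 16.4 | 86% | 6.0 | 51% |
| 0.5 | 0.4 | 12.2 | 73% | 8.2 | 65% |
| 0.5 | 0.6 | 18.4 | 91% | 6.7 | 56% |

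A test of EPDS itself rejects in 5% of the same trials. With all 129 per arm retained, the group-by-time rate is 85% to 98%.

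**One scale only.** If SICS alone improves by 0.35 SD, s = 0.35²(1 + r)/[(1 − r)(1 + 2r)], which is 0.142 for r = 0.3 and 0.184 for r = 0.5. The test then rejects in 46% to 79% of trials (group by time) or 34% to 52% (group). With every effect zero, each test rejects in 5%, so the MANCOVA is valid for its own joint null. The difficulty is only in what its rejection is said to show.

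**The case against.** The strongest reply is that this is a condensed article. Section 3.2.8 names a model and states no decision rule, and per-scale follow-up tests may be in a full protocol or analysis plan that is not shown. If they are, EPDS would be examined on its own and the rates above would not turn into false depression claims. That stands as a limit on the consequence, and the absence of follow-up tests is not the finding. The finding is that the article does name a deciding test and attaches three outcome-specific conclusions to it, which that test cannot deliver.

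Three stronger readings are tempting and are not supported.

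- A reader might infer that the MANCOVA is at fault for ignoring direction, since SICS is scored so that "A higher SICS score means a higher level of" self-efficacy while a higher EPDS is worse. But any two-sided t test or model contrast also rejects equally often for equal benefit and harm, and direction is read from the estimate. Only the joint null is particular to this method.
- A reader might infer that the MANCOVA has little power for an EPDS effect of 0.35 SD at post-test 1 only. The group main effect has just 11% to 15%, but the group-by-time test has 46% to 79%, against 65% for a t test. As the article does not say which effect is meant, a general loss of power is not shown.
- A reader might infer that the plan will make a false depression claim in 67% to 91% of trials. That needs the assumed correlations, the assumed effects on the other two scales, and reliance on the omnibus result alone.

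**Conclusion.** The concern holds in this form. The test named in section 3.2.8 has a null that is joint over scales and times, so rejecting it cannot support a separate claim for self-efficacy, social support or depression, nor say when a change occurred. It also does not test the EPDS difference on which section 3.2.2 sizes the trial. This follows from the form of the test and needs no numerical assumption.

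The size does rest on assumptions. Under those listed, with no EPDS effect, the omnibus test rejects in 67% to 91% (group by time) or 51% to 65% (group) of trials, against 5% for EPDS's own test. These are error rates for a depression claim only if the omnibus result is used as its evidence, as the sentence is worded.

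**What to change.** In section 3.2.8, rest each outcome claim on that scale's own between-arm contrast from a baseline-adjusted model (ANCOVA, or a mixed model for repeated measures). Report the adjusted difference with its sign and 95% CI. Name one deciding time point and make the other supportive; section 3.2.3 already groups post-test 1 with the primary endpoints and calls post-test 2 a follow-up measure. Base the depression claim on EPDS, to match section 3.2.2.

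Control multiplicity over the three scales, for example by Holm, or by a fixed sequence starting with EPDS. Without such a rule, three independent tests at 0.05 carry a family-wise error of 1 − 0.95³ = 14.3%, and six (three scales at two times) carry 1 − 0.95⁶ = 26.5%. Keep the MANCOVA, if wanted, as a supportive global test or gate that licenses no outcome-specific claim.

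The cost is analysis wording: same data, same software, no added visits. The downside is that scale-specific results under multiplicity control replace one global p value, and some scales may not reach significance. At 90 per arm, a two-sided EPDS t test for 0.35 SD has 65% power. Baseline adjustment raises this to 72% to 83% under the assumed correlations over time of 0.4 to 0.6. Those figures are at alpha 0.05, which a fixed sequence starting with EPDS preserves for that scale.
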